## Abstract

**Background:**

Mental disorders are highly prevalent, and they significantly impact individuals and society. Patients experiencing long-term, severe mental disorders with functional impairment and reduced quality of life often have a history of adolescent onset anxiety and depressive disorders. Despite the long-term costs to both patients and society, studies examining treatment effects over time and across diagnoses are scarce.

**Objective:**

The Norwegian Adult Mental Health Registry (NAMHR) aims to systematically reuse health data to monitor and improve treatment outcomes, patient safety, health service quality, and research. The registry addresses the need for comprehensive data on the effects and utility of mental health services, interventions, and therapy variants in specialized mental health care.

**Methods:**

The NAMHR is a nationwide naturalistic registry, including all Norwegian adults eligible for treatment in specialized mental health care services who have not opted out. Patients are automatically enrolled when treated in these services. The population includes patients treated in public specialized services and those treated in private services having a contract with public health services. The registry is based on secondary data from the Norwegian Patient Registry (NPR), patient-reported outcome measures (PROMs), patient-reported experience measures (PREMs), the Norwegian Registry for Primary Health Care (KPR), and several other sources, including electronic health records (EHRs). Data linkage uses unique national identity numbers, ensuring high-quality data. The registry collects information on diagnoses, treatments, medication, and patient-reported outcomes, providing a holistic approach to mental health care. Statistical analyses will be defined in each project.

**Results:**

As of December 2025, the NAMHR is approved and is being constructed. The registry anticipates enrolling up to 170,000 participants, with a new incidence rate of around 10,000 patients per year. Key predictors and outcomes include PROMs and PREMs, and automatically reported measures involving a wide range of data, including EHR data from inpatient and outpatient treatments, data from primary health care, data on job and education status, and data on cause of death. Enrollment is planned to start in 2026, initially by adding journal data and patient-reported data. Other sources will be included. The NAMHR has no planned end date. Results will be made available for internal quality improvement purposes, and data for research are expected to be available around mid-2026 for approved projects.

**Conclusions:**

The NAMHR will promote quality improvement initiatives and research, including registry-based randomized clinical trials. It will also be possible to link the NAMHR to a similar registry for children and adolescents, making it possible to follow patients from birth to death and supporting the monitoring of diagnostic drift. The NAMHR will inform health policy decisions at local, regional, national, and international levels, contributing to the evaluation and development of clinical guidelines and enhancing personalized treatment approaches.

## Introduction

Although mental disorders are highly prevalent and impact the lives of affected individuals and their next of kin, transdiagnostic nationwide quality-improvement programs are scarce. Two-thirds of mental disorders occur before the age of 25 years [1,2]. In both high-risk populations and the general population, mental disorders that develop in adolescence persist into adulthood, cause functional impairment, and reduce quality of life [3,4]. Mental disorders now account for at least 45% of the overall disease burden in those aged 10‐24 years [5,6] and represent a substantial burden at the societal level [7]. Early onset is associated with a longer duration of illness and additional comorbid disorders [8]. In particular, anxiety and depressive disorders rank high with regard to nonfatal health issues [9].

A quality registry is a systematic collection of data used to monitor and improve treatment outcomes, patient safety, and health service quality. In Norwegian national quality registers, the term “quality” especially refers to data accuracy, reliability, and relevance. To ensure a high level of data quality, the data must be complete, consistent, and up to date. A registry with good data, relevant measures, and relevant and accessible reports offers opportunities for policy makers, service managers, and researchers. Good quality also entails the active use of registries in health service improvement and innovation. The Norwegian Adult Mental Health Registry (NAMHR) will merge nationwide data sources, including patient-reported data, and is expected to provide new and unique data for both quality improvement and research. The data from the registry will contribute to the identification of variations in practice and the assessment of whether health services meet established quality criteria.

Established quality criteria include high effectiveness and safety, user involvement, resource coordination and utilization, high accessibility, and fair distribution. The NAMHR will provide clinicians and leaders with updated and accessible information on the effects and utility of health services, including specific interventions, therapy variants, and compulsory treatment use. This is important as specialized mental health care faces several challenges, and mental disorders are already the most expensive category of disorders in Norway [10,11].

The extent to which evidence-based clinical guidelines are implemented in daily clinical practice for specialized mental health care is unknown, and thus, it is difficult to monitor unwarranted variation [12]. Currently available data in Norway report on patient rates, admission rates, bed days, number of consultations, variation in staff specialities, rejected referrals, and waiting times. There is little information on patients’ perspectives. Although the volume, expertise, and availability of treatment are increasing, little is known about the effects of these increases on patients’ outcomes in the short and long term. There is a national need to follow patients’ pathways and progress; demonstrate and document treatment outcomes and effectiveness; perform quality control evaluations of treatment outcomes and effectiveness; and determine how treatments lead to changes in patients’ symptoms, functioning, and quality of life [13]. Furthermore, there is a need to uncover unwarranted variance across units, hospitals, and health regions. For example, a report from 2023 on attention-deficit/hyperactivity disorder (ADHD) diagnosis revealed large between-clinic variation in the incidence rate of ADHD [14].

Further adding to the importance of quality control is the evidence of increasing rates of mental disorders, including anxiety, depressive symptoms, psychological distress, self-harm, and suicide, among young people since early 2010 [15-21]. A recent Australian study of mental health and well-being (2020‐2022) revealed a 50% increase in mental disorders at the diagnosis level among people aged 16‐24 years since 2007, with an annual prevalence rate of 39% from 2020 to 2022 [16]. Similar but weaker tendencies are found in Norway, as reported in the SHOT Study (Students’ Health and Wellbeing Study) [22] and HUNT Study (Trøndelag Health Study) [23]. The presence of mental disorders among young people is a largely ignored risk factor for age-related medical illnesses [24]. The lifetime risk in a population that meets the criteria for a diagnosable mental disorder is estimated to be 50% [25]. If these disorders are not treated, they can become major causes of reduced quality of life, high costs to the family, and high disability-adjusted life years [26]. Suicide remains the fourth most common cause of death among people aged 15‐29 years globally [5], and mental disorders are some of the most frequent reasons for visits to general practitioners. Patients with mental disorders have 5‐15 life-years lost (LYL) [27], and patients with serious mental illnesses, such as schizophrenia, have 9‐12 LYL [28]. The most common causes of death overall are natural causes, such as cardiovascular diseases and cancer, many of which are preventable and treatable [29].

In real-life clinical psychiatric settings, it is relatively common for diagnoses to change over time. An individual receiving an anxiety diagnosis in early adolescence might be assessed as having depression in late adolescence before being diagnosed with schizophrenia in their mid-20s. Adding to this, the diagnostic criteria themselves have changed, including the *Diagnostic and Statistical Manual of Mental Disorders* (*DSM*) [30] and the *International Statistical Classification of Diseases and Related Health Problems* (*ICD*) [31]. The individual diagnostic “drift” and criteria “drift” highlight the importance of transdiagnostic quality registers. Diagnostic drift also highlights the importance of incorporating new models or frameworks in specialized mental health quality control, and a suitable model is clinical staging. The clinical staging model [32-36] (Figure 1) presents a new and important longitudinal perspective. Clinical staging is congruent and synergistic with many developmental and related conceptual frameworks and allows for exploring mechanisms underpinning the onset and course of mental disorders. The clinical staging model places people along a multidimensional continuum from health to illness in order to capture elements of risk, onset, course, and prognosis. This transdiagnostic model [32,36-38] recognizes the fluid nature of mental disorders and distinguishes between early clinical stages (with low rates of progression to more severe disorders) and later stages (with higher rates of persistence and impairment).

**Figure 1. F1:**
[figure not shown]
Heuristic clinical staging model for mental disorders (reproduced with permission from McGorry and Mei [36]).

The model illustrates clusters of early symptoms (microphenotypes) and their potential progression into clear and often comorbid syndromes (macrophenotypes). This progression across stages is characterized by increasing symptom severity, specificity, and disability (represented by the sphere size; the spheres and colors represent phenotypes).

The clinical staging model is suitable as an overarching framework for the NAMHR to guide the ongoing selection of unwarranted variations to monitor. Currently, even established diagnostic-specific Norwegian care pathways [39] lack implementation studies. These care pathways specify time frames for assessment, treatment, and clinical evaluation and are based on previous findings that show positive prognostic effects of early diagnosis and treatment [40]. In line with clinical staging, the purpose of care pathways is to improve services across functions, activities, and units, as well as the wider health and welfare service system. The care pathway packages follow the same principles as those previously implemented for cancer [41]. Collecting data on care pathways enables the NAMHR to observe continuous chains of treatment and follow-up across service providers and to provide data on unnecessary delays in assessment, treatment, care, and follow-up in order to contribute to equal quality of care across geographical regions. Findings from several care pathways may provide data for a more overarching model like the clinical staging model. For example, poor coordination of medical health care has been associated with early mortality and a lack of physical health checks, prescriptions, and medical procedures [42-44]. More importantly, it is unknown whether and to what extent care pathways improve mental, medical, and functional outcomes. Additionally, there are no current national quality indicators that measure patients’ mental health treatment outcomes, and such indicators are not linked to the degree of compliance with care pathways.

Patient-reported measures are important in health care in general, but patients’ own experiences are especially important in mental health care as mental disorders manifest as challenges and disturbances in the experience of oneself and the world. In research settings, standardized and validated self-report measures often define outcomes. In mental health care, other outcomes, such as diagnoses and waiting times, are more frequent. The systematic collection of patient-reported outcome measures (PROMs) [45] and patient-reported experience measures (PREMs) [46,47] is increasing. The PROMs subgroup of routine outcome monitoring (ROM) involves clinical data primarily intended as part of a medical journal for individual documentation and treatment. Great Britain’s public health services have used such ROM data to document treatment effects [48,49] at the individual level. However, aggregated ROM data may be used as process measures in quality registries to detect unwarranted variations. Overall, the patient perspective is emphasized as an important aspect of quality in health services. To enhance the patient perspective, the National Mental Health Service Organization (Mental Helse Norge [50]) participated in the development of the NAMHR and has 2 members on the advisory board. The patient perspective includes the patient’s satisfaction with treatment and provides subjective measures of effect and change. In mental health care, several PROMs are at a level of precision to be accepted as outcome variables in a quality registry [48], but are not sufficiently used at the system level. In Norway, this need is highlighted in the government’s (Stortinget’s) report on quality and patient safety [51].

The NAMHR’s purpose is to provide a platform for transdiagnostic, nationwide quality improvement. One such issue is increased knowledge of “personalized treatment” in adults (eg, what works, when, where, in what way, and for whom). This is primarily fulfilled by facilitating the statutory duty for quality improvement that specialist health care providers have, and secondarily by delivering data for research. Specialized mental health care services in Norway are divided into child and adolescent services and adult services, resulting in 2 separate registers. Given the abovementioned importance of early interventions and longitudinal perspectives, this is suboptimal. However, as both registers have a common system architecture, ethically approved research studies may use merged data, following individuals from birth to death.

## Methods

### Study Design

The sample will include individuals who have been referred to specialized mental health care services and have not opted out. As individuals may be included at any time and included individuals may file reservations (opt out) at any time, both the population size and sample size will vary. The total population was approximately 170,000 participants as of 2023 [52]. The population includes patients treated at public specialized mental health care services and similar private services having a contract with public health services (contract specialists). Mental health services funded outside public health services (eg, privately or through insurance) are not considered. According to the South-Eastern Norway Regional Health Authority (the largest of the Norwegian health authorities), only 1% of licensed health personnel were working in private specialized health services in 2025 [53], which indicates that the vast majority of specialized health care services are funded publicly in Norway. According to the Norwegian Patient Registry (NPR) [54], the yearly treated incidence rate is estimated at approximately 10,000 patients. The start of data collection has been planned for autumn 2025. Patients treated prior to the start will be considered as new cases, resulting in an initial overestimation of incidence rates. The degree of registry coverage is defined as the number of nonreserved participants divided by the number of eligible participants. The coverage is currently unknown as neither data collection nor reservation has started. The NAMHR anticipates similar coverage as that of the reservation-based Norwegian Diabetes Register for Adults, which reported a nationwide coverage of 88% in 2023 [55].

The NAMHR was approved in late 2023 and is designed as a national naturalistic follow-along study based on all Norwegian adults eligible for treatment in specialized mental health care services, who have not opted out of participation (detailed inclusion and exclusion criteria are provided below). This protocol is compliant with the standards outlined in the SPIRIT (Standard Protocol Items: Recommendations for Interventional Trials) 2013 Statement [56]. The SPIRIT checklist is provided in Checklist 1. The trial is registered at ClinicalTrials.gov (NCT06115200) [57,58].

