### Outcomes: Quality Indicators

The purpose of the national quality indicator system [61] is to ensure equal access to good-quality health services for the population based on the framework of the Health Care Quality and Outcomes program of the Organisation for Economic Co-operation and Development [62-64]. The national quality indicators serve several purposes: (1) they provide central health authorities with a basis for monitoring, prioritization, and management; (2) they provide managers at all levels with a basis for quality improvement; and (3) they contribute to public transparency on quality and variation in services.

The NAMHR’s quality indicators are dynamic, as they aim to reflect quality challenges in mental health care for adults at any given time. The register’s proposed quality indicators (Table 1) are based on and comply with recommendations in national guidelines. As of 2025, in Norway, there are five national guidelines in the field of mental health (adults): (1) National professional guidelines for ADHD/hyperkinetic disorder [65]; (2) National professional guidelines for the prevention of suicide in mental health care [66]; (3) National professional guidelines for the early detection, assessment, and treatment of eating disorders [67]; (4) National professional guidelines on the use of electroconvulsive therapy [68]; and (5) Guidelines on psychotic disorders and medications [69].

**Table 1. T1:** Initial Norwegian Adult Mental Health Registry quality indicators.

Overarching theme and quality indicator (measure)		Type	Expected level for the measure
Examination and diagnostics			
Proportion of incident (new) patients diagnosed with structured diagnostic instruments (eg, SCID-CV^a^ and MINI^b^ 7.0.2)		Process	≥90%
Somatic health and cardiovascular risk			
Proportion of incident (new) patients whose BMI is measured		Process	≥90%
Proportion of incident (new) patients whose lipid and HbA_1c_ levels are measured		Process and results	≥90%
Proportion of incident (new) patients whose blood pressure is measured		Process and results	≥90%
Outcome/results			
Proportion of patients who use the mental health feedback tool for adults		Process and results	≥90%
Similar results for comparable groups (CORE-OM^c^) [70]		Results	Group difference in improvement >5 points
Improved quality of life (WHODAS^d^) [71]		Results	Share of participants who report improved quality of life

a SCID-CV: Structured Clinical Interview for *DSM-5*, Clinician Version.

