Textbox 1.Example structural, process, and outcome variables in the Norwegian Adult Mental Health Registry.Predictor variables (independent); individual and structural levelsSymptoms and function at baseline; patient-reported outcome measures (PROMs) (Clinical Outcomes in Routine Evaluation–Outcome Measure [CORE-OM], Alcohol Use Disorders Identification Test [AUDIT] [72], and Drug Use Disorders Identification Test [DUDIT] [73])Age (Norwegian Patient Registry [NPR]) and gender (NPR)Referral date (NPR)Assessment date (NPR)Start date, both outpatient and inpatient (NPR)Unit name and description (NPR)Prior referral/treatment (NPR)Prior episode of compulsory mental health care (NPR)Suicide assessment (NPR)System-level variables, such as turnover, tenure, percentage of doctors who are psychiatrists, percentage of psychologists with relevant specializations, and number of available hospital roomsProcess variables; individual levelSymptoms and function at multiple times during treatment; PROMs (CORE-OM, AUDIT, and DUDIT)Hours spent on outpatient treatmentEnd date (NPR)Duration of treatment (NPR)Use of structured symptom and function assessment instruments (NPR)Structured codes for diagnoses and procedures from the national patient registry (NPR)Quality of life assessment (World Health Organization Disability Assessment Schedule [WHODAS])Ongoing compulsory mental health care (NPR)Suicide assessmentType of given treatment, standardized procedure codes (NPR)Somatic: blood pressure, height, weight, and other relevant tests (electronic health record [EHR])Medication: type, administration, dosage (Norwegian Prescribed Drug Registry [NorPD])System-level variables, such as turnover, tenure, percentage of doctors who are psychiatrists, percentage of psychologists with relevant specializations, and number of available hospital roomsResult variables (outcome); individual and structural levelsSymptoms and function at discharge; PROMs (CORE-OM, AUDIT, and DUDIT)PROMs, quality of life change (WHODAS)Patient-reported experience measures; overall satisfaction with mental health care (Pasient Opplevelser - patients’ satisfaction with treatment [PASopp])Mortality rate and cause of death (Norwegian Cause of Death Registry [NCDR])Outcome measures regarding primary care follow-up, such as individual treatment plan, general practitioner assessment, municipality coordinator, type of work, and ongoing education (Norwegian Registry for Primary Health Care [KPR])Compulsory mental care as part of aftercare (NPR)Suicide assessmentMedication type, administration, and dosage in epicrisis on discharge (EHR and NorPD)

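### Counting earlier-treated patients as new cases mixes new and prevalent patients in four Table 1 denominators, while the protocol acknowledges only the effect on incidence

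*Protocol article*

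**What the plan says.** The Study Design section states the rule for patients already known to the services: "Patients treated prior to the start will be considered as new cases, resulting in an initial overestimation of incidence rates". The same section gives the size of the population ("The total population was approximately 170,000 participants as of 2023") and, citing the NPR, the inflow ("the yearly treated incidence rate is estimated at approximately 10,000 patients").

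Table 1, under Outcomes: Quality Indicators, lists seven indicators. Four are proportions of incident (new) patients: diagnosis with a structured instrument, BMI ("Proportion of incident (new) patients whose BMI is measured"), lipids and HbA1c, and blood pressure. Each has an expected level of at least 90%. Neither the table nor its text defines incident (new), sets a look-back or wash-in period, or gives a time window for the measurement.

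The Data Sources section names the NPR as the main source and says that it carries timestamps on episodes of care. Textbox 1 lists prior referral or treatment, taken from the NPR, among its example predictors.

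The start that separates earlier from new is given in two ways. Study Design says "The start of data collection has been planned for autumn 2025". The Results paragraph of the abstract says "Enrollment is planned to start in 2026, initially by adding journal data and patient-reported data".

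**The concern.** The rule makes new mean new to the registry. The article accepts the consequence for incidence rates and calls it initial, but it is silent on the four indicators that share the same word. A reader of Table 1 would take each of them as a statement about people entering specialized care. Under the Study Design rule, an unknown and possibly large part of the denominator would be people already in care, or treated before, when the registry opened.

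The registry exists to detect unwarranted variation between units, hospitals and regions. The Dissemination Plan sends monitoring results to a dashboard for the services, and the Statistical Analysis section mentions statistical process control over time. If the share of earlier-treated patients differs between units or changes over calendar time, and compliance differs between the two groups, a difference in denominator mix could be read as a difference in quality.

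**Working it through.** **Inputs from the protocol article (Study Design).** Total population 170,000; yearly treated incidence I = 10,000; anticipated coverage 88%, borrowed from a diabetes register ("which reported a nationwide coverage of 88% in 2023"). The first two are cited, not derived, so there is no calculation in the plan to reproduce.

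**Inputs that are assumptions.** f, the share of earlier-treated patients who enter in the first period and are counted as new; p, compliance with an indicator among truly new patients; q, compliance among earlier-treated patients.

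**Step 1. Composition of the denominator.** If the 170,000 includes the new patients, the earlier-treated pool is P = 170,000 − 10,000 = 160,000. The denominator is D = I + f × P, the earlier-treated share is f × P / D, and the overstatement of incidence is D / I.

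| f | D | Earlier-treated share | Incidence overstated |
|---|---|---|---|
| 0.05 | 18,000 | 8,000/18,000 = 44% | 1.8-fold |
| 0.10 | 26,000 | 16,000/26,000 = 62% | 2.6-fold |
| 0.25 | 50,000 | 40,000/50,000 = 80% | 5-fold |
| 0.50 | 90,000 | 80,000/90,000 = 89% | 9-fold |
| 1.00 | 170,000 | 160,000/170,000 = 94% | 17-fold |

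The last row is an upper bound. If the 170,000 excludes the new patients, it becomes 170,000/180,000 = 94.4% and 18-fold.

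**Step 2. Coverage.** At 88%, D for f = 1 is 149,600 and the truly new number 8,800. The ratio is still 17, so coverage leaves the shares unchanged unless opting out differs between the groups.

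**Step 3. Effect on an indicator.** Observed value = (I × p + f × P × q) / D.

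- f = 1, p = 95%, q = 20%: (9,500 + 32,000)/170,000 = 24%.
- f = 1, p = 95%, q = 60%: (9,500 + 96,000)/170,000 = 62%.
- f = 0.05, p = 95%, q = 20%: (9,500 + 1,600)/18,000 = 62%.
- f = 0.05, p = 95%, q = 60%: (9,500 + 4,800)/18,000 = 79%.
- Value of q needed to read 90% at f = 1, p = 95%: (153,000 − 9,500)/160,000 = 89.7%.

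**Step 4. The opposite direction.** With f = 1, p = 85% and q = 95%, the indicator reads (8,500 + 152,000)/170,000 = 94%. It would pass although new patients fall short. The sign of the error therefore depends on whether q lies below or above p, and the article gives neither.

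**The case against.** The strongest reply is that the article discloses the incidence bias openly and calls it initial. Applying the Study Design rule to Table 1 is an inference, because the table does not refer back to it. The indicators are described as initial, proposed and dynamic, the variable lists as tentative, and an article may leave denominator definitions to the full protocol. Part of this stands: the incidence bias is not hidden. But the rule is stated, not omitted. It is the only text that says who is new, and a reader applying the article to Table 1 has no other definition to use.

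Several stronger readings are tempting, and the documents do not support them.

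- That earlier-treated patients necessarily count as failures because their entry work-up is over. Table 1 sets no time window. The Data Sources and Process Variables sections also reuse previously collected health-record data, including BMI and blood pressure, so these patients could score lower or higher than new ones.
- That the indicators will drift upward and imitate improvement. This needs q below p, which is not established.
- That the registry already holds the prior-treatment variable. It is listed as an example; data collection has not started, and the depth of the look-back is not stated.
- That patients arriving from the child and adolescent registry are misclassified. Counting first entry to adult care as incident is a legitimate choice, provided that it is stated.
- That wrong indicators will be published in mid-2026. That date is given for data availability, not for these four figures.

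**Conclusion.** The point holds for the definition. The rule as written puts earlier-treated patients into an incidence series and, with no other definition in the article, into four of seven indicator denominators labelled as incident (new). The article acknowledges only the first consequence.

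The composition figures rest on the plan's own 10,000 and 170,000 and on the share who enter: 44% earlier-treated and 1.8-fold incidence at 5%, up to 94% and 17-fold if all enter in one period. The misclassification is thus material even at low carry-over.

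The effect on the indicator values is not established in size or direction. The range of 24% to 62% is a worst case for composition, with assumed compliance of 95% in new and 20% to 60% in earlier-treated patients. It illustrates sensitivity and is not a forecast.

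The two start dates leave the cut-off in the rule unfixed. That is a smaller point and does not change the conclusion.

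**What to change.** Replace the Study Design rule with a definition: an incident patient is one with no specialized mental health episode in the NPR during a fixed look-back before the referral date, of the same length for every calendar year. Then:

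- use this definition for the incidence series and for the four Table 1 denominators, and refer to it in the table;
- flag all other patients as prevalent and keep them out of those figures;
- withhold the figures, or mark them as provisional, until the NPR is linked, since journal and patient-reported data are to be loaded first;
- state whether contacts with child and adolescent services count as earlier episodes;
- reconcile the start date between Study Design (autumn 2025) and the abstract (2026).

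The cost is protocol wording and one derived variable from a source already in scope. With the definition in place, the yearly denominator returns to about 10,000, or about 8,800 at 88% coverage. The downsides are some residual misclassification of patients last seen before the look-back, and smaller denominators in the first year. The change is cheapest now, before collection starts; later it would mean restating any figures already released.
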